### Interventions

#### Explanation for the choice of comparators {6b}

Participants are randomized on a 1:1 ratio into an experimental group and a control group. The experimental group receives NMES plus EMG biofeedback-mediated PFMT. The control group undertakes conventional PFMT [13] alone. Conventional PFMT is also included for the experimental group to ensure a sufficient frequency of PFMT, as 2–3 days a week of PFMT is often recommended for effective resistance training [23, 30]. The total frequency and time of PFMT are equal between groups.

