#### Intervention description {11a}

As the latest guidelines for UI management recommend muscle training for at least 12 weeks, we set our intervention length as 12 weeks [23, 30].

In the baseline visit, all participants (regardless of group allocation as conventional PFMT is required for both) will receive a one-to-one education session. During this session, we brief them on the functional anatomy of PFM, assess their PFM contractive ability, and teach them the correct exercise technique. Timely feedback from the physiotherapist enhances their sensation of self-muscle activity and optimizes their training effectiveness by avoiding common mistakes, such as co-contraction of abdominal, deep hip, and thigh muscles. An individualized home-based PFMT program is prescribed for each according to their baseline PFM function. Evaluation and instruction are carried out in line with the PERFECT scheme (Power, Endurance, Repetitions, Fast, Every Contraction Timed). The initial resistance training program is as follows:
Lift PFM upwards and inwards and squeeze the vagina, urethral and anal sphincters, as hard as they can without disturbing their breathing rhythmHold it for 3–5 s before relaxing the muscles gently for the same time interval (3–5 s). Depending on individual ability, the time interval usually starts from 3 s and progresses to 5 s 4 weeks after and 5 s by the end of the interventionRepeat the sequence ten times in one set and perform three sets a day

During the intervention period, frequency measured as times per week differs between groups, as conventional PFMT mainly serves as a supplement to instrumented PFMT for the experimental group. We recommend the same frequency of 3 days a week after the intervention period ends.

After the baseline visit, women in both groups will also get an electronic or printed manual with their personalized PFMT program, emergency contact, and lifestyle advice, such as avoidance of heavy lifting besides breastfeeding and maintenance of unobstructed defecation.

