#### Control group: conventional PFMT

Participants assigned to the conventional PFMT group will perform the prescribed program 3 days a week for the entire intervention period. After each self-managed home-based PFMT session, participants are required to upload a record (note), detailing their contraction and relaxation time for each contractive sequence, repetition of sequences and sets, onto a system checked and responded by physiotherapists on a daily basis. Such recording improves adherence to the intervention, and thereby the control group would acquire the same amount of contact and supervision from medical staff with the experimental group.

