#### Experimental group: NMES plus EMG biofeedback

NMES and EMG biofeedback will be performed 24 sessions, two weekly sessions of 30 min with MyoTrac Infinti Encoder (Model SA9800, Thought Technology Ltd., Canada) equipment, which contains two channels for EMG collection, channel A for PFM and channel B for rectus abdominis. NMES is delivered through electrodes on the RAYEE-A Vaginal Probe (Nanjing Vishee Medical Technology Ltd., China). Muscle electrophysiology is collected through electrodes on the same probe at a 14-bit resolution and a 2048-Hz sampling rate. The electric parameters are current type: functional electrical stimulation; frequency: 30–50 Hz; pulse duration: 300–500 μs; time: 10 min; 4–10s cycles; rise: 2–5 s fall: 2–5 s; and stimulation intensity: maximal level tolerable [7, 16]. Participants will be instructed to not actively contract pelvic floor muscles during the electrical stimulation and then perform PFMT following the visual instruction for 15 min. Two NMES and EMG biofeedback-mediated PFMT programs and one conventional PFMT program (see the above section) per week (with 3 PFMTs dispersed in 3 separate days) are arranged for the experimental group to ensure the same total amount of pelvic floor muscle training between two groups.

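### The protocol states that PFMT time is equal in both arms, but its written schedule gives the experimental arm more PFMT minutes, so a benefit cannot be credited to NMES and biofeedback as distinct from more training time.

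*Protocol article*

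**What the plan says.** Equality between the arms is stated twice in the protocol article. Under Explanation for the choice of comparators {6b}: "The total frequency and time of PFMT are equal between groups". Under Experimental group: NMES plus EMG biofeedback, the weekly mix of sessions is arranged "to ensure the same total amount of pelvic floor muscle training between two groups".

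The schedule itself is spread over three sections:

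- **Home programme** (Intervention description {11a}): a contraction is held for 3 to 5 s and followed by relaxation of the same length. Participants repeat "the sequence ten times in one set and perform three sets a day". The protocol calls this the initial programme and individualises it. The interval usually starts at 3 s and reaches 5 s after 4 weeks.
- **Control arm** (Control group: conventional PFMT): participants "will perform the prescribed program 3 days a week for the entire intervention period".
- **Experimental arm** (Experimental group: NMES plus EMG biofeedback): "NMES and EMG biofeedback will be performed 24 sessions, two weekly sessions of 30 min". Each session has 10 min of stimulation, during which participants are told not to contract. They then "perform PFMT following the visual instruction for 15 min". One conventional home programme a week is added, so that training falls on three separate days.

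The intervention lasts 12 weeks.

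**The concern.** The claim names time as well as frequency, so matching the number of training days does not satisfy it. The minutes can be worked out from the protocol's own figures, and they differ in favour of the experimental arm.

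The statement matters because the background section hypothesises that NMES-combined PFMT is superior through better modulation of the pelvic floor muscle, and the discussion hopes to support wider use of NMES and biofeedback. Equal training is the premise that would let a benefit be assigned to the devices. If the experimental arm also trains for longer, the devices and the extra training are confounded by design. A reader who relies on the equality statement would then draw a conclusion that the design cannot support.

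**Working it through.** **Inputs.** Hold *s* = 3 to 5 s with relaxation of the same length, 10 repetitions, 3 sets a day (Intervention description). Control: 3 home days a week (Control group section). Experimental: 2 guided blocks of 15 min and 1 home day a week (Experimental group section). Duration: 12 weeks. Stimulation time is not counted as PFMT because active contraction is ruled out during it.

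**The plan's figure.** Equal time means a ratio of experimental to control minutes of 1.0.

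**Formulas.**
- Home day: h = 3 × 10 × 2*s* / 60 min
- Control per week: 3h
- Experimental per week: 2 × 15 + h
- Ratio: (30 + h) / 3h

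| Interval | Home day h | Control/week | Experimental/week | Ratio |
|---|---|---|---|---|
| 3 s | 3 min | 9 min | 33 min | 33/9 = 3.67 |
| 4 s | 4 min | 12 min | 34 min | 34/12 = 2.83 |
| 5 s | 5 min | 15 min | 35 min | 35/15 = 2.33 |

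No interval from 3 to 5 s gives a ratio of 1.

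**Twelve-week totals.** The progression is taken as a step, 3 s for 4 weeks and 5 s for 8 weeks (an assumption about its shape):
- Control: 4 × 9 + 8 × 15 = 156 min
- Experimental: 4 × 33 + 8 × 35 = 412 min
- Ratio: 412/156 = 2.6

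**Sensitivity to rest between home sets.** The protocol states none. Three sets have two gaps, so a rest of *r* min per gap gives h = 3 + 2*r* at 3 s, or 5 + 2*r* at 5 s.

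| Interval | Assumed rest per gap | h | Ratio |
|---|---|---|---|
| 3 s | 1 min | 5 min | 35/15 = 2.33 |
| 3 s | 2 min | 7 min | 37/21 = 1.76 |
| 5 s | 1 min | 7 min | 37/21 = 1.76 |
| 5 s | 2 min | 9 min | 39/27 = 1.44 |

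**What equality would need.** If a guided block contains *w* minutes of training, the ratio is (2*w* + h) / 3h, which equals 1 only when *w* = h. There are two ways to get there:
- The home day lasts 15 min, which needs (15 − 5)/2 = 5 to (15 − 3)/2 = 6 min of rest in each gap.
- Only 3 to 5 of the 15 guided minutes are training, which leaves 10 to 12 idle beyond the relaxation between contractions.

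The protocol states neither.

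**The case against.** The strongest case on the other side has five parts.

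1. *Unlike quantities are compared.* Home time is net contract-and-relax time. The guided figure is a 15-minute block whose work and rest pattern is not given. This stands as a limit on the multiple, and the sensitivity table shows how far it can fall. It does not restore equality.

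2. *The home programme is only a starting point.* It is individualised, therapists adjust it at appointments, and the Knack maneuver is added once strength reaches grade 3. Carrying 30 contractions a day through 12 weeks is therefore an assumption. However, the protocol gives both arms the same appointments and does not say that adjustment brings a home day to 15 minutes.

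3. *A ratio of 3.7 is too high for the trial as a whole.* This stands. The figure holds only while the interval is 3 s, which under the stated progression means the opening weeks.

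4. *Frequency is not contradicted.* A reader might take the remark that "frequency measured as times per week differs between groups" as a flat contradiction of the equality claim. In context it refers to conventional sessions, 3 a week against 1. Total training days are 3 in each arm. The phrase on total amount follows directly on the count of three sessions and could be read as a session count. The word time in the comparator section cannot be read that way.

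5. *The trial already compares packages.* The objective sets assisted PFMT against conventional PFMT, and the discussion contrasts instrument-based training with self-management. A reader might infer that unequal minutes invalidate the trial or its cost-effectiveness analysis. The documents do not support that. The randomised contrast between the two programmes is intact, and an incremental cost-effectiveness ratio compares costs and effects of each programme as delivered, which does not require equal minutes.

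**Conclusion.** The concern holds in a limited form. Equal PFMT time is a stated design property that the schedule does not have. On the initial programme the weekly minutes are about 9 to 15 in the control arm and 33 to 35 in the experimental arm. The best single summary is a 12-week ratio of about 2.6, which rests on a stepwise progression, no rest between home sets, a fully used 15-minute guided block and no later change to the number of contractions. Rest of 1 to 2 minutes per gap would put the ratio at about 1.4 to 2.3. The size is therefore uncertain, but no reading of the written figures gives equality without long idle periods that are not stated.

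What falls is narrow: a benefit could not be assigned to NMES and biofeedback as distinct from more PFMT time. A difference between the two programmes, and its cost-effectiveness, can still be estimated. The statement should be corrected, but this is not a fatal flaw in the design.

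**What to change.** Reconcile the comparator rationale, the intervention description and the two group descriptions so that they give one consistent account of PFMT time per arm. Which schedule is right is for the investigators to decide.

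Unless the reconciled schedule gives equal minutes:

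- Delete the statements of equal time and equal amount. Equal training days can stay.
- State that the arms also differ in PFMT minutes.
- Limit attribution to the package, that is, NMES with biofeedback-guided training plus one home day against home PFMT.
- Report delivered PFMT minutes by arm in a descriptive table.

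It would also help to make clear that the remark on differing frequency refers to conventional sessions only.

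The cost is a narrower attribution claim and some added recording. Uploaded training records are described only for the control arm, so the experimental arm's home day and guided minutes would have to be entered in the same system. The Trial status section reports 75 women already enrolled at the first centre, and for them the experimental arm's minutes may be incomplete. Randomisation, the primary outcome and its analysis do not change.

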#### Intervention description {11a}

As the latest guidelines for UI management recommend muscle training for at least 12 weeks, we set our intervention length as 12 weeks [23, 30].

In the baseline visit, all participants (regardless of group allocation as conventional PFMT is required for both) will receive a one-to-one education session. During this session, we brief them on the functional anatomy of PFM, assess their PFM contractive ability, and teach them the correct exercise technique. Timely feedback from the physiotherapist enhances their sensation of self-muscle activity and optimizes their training effectiveness by avoiding common mistakes, such as co-contraction of abdominal, deep hip, and thigh muscles. An individualized home-based PFMT program is prescribed for each according to their baseline PFM function. Evaluation and instruction are carried out in line with the PERFECT scheme (Power, Endurance, Repetitions, Fast, Every Contraction Timed). The initial resistance training program is as follows:
Lift PFM upwards and inwards and squeeze the vagina, urethral and anal sphincters, as hard as they can without disturbing their breathing rhythmHold it for 3–5 s before relaxing the muscles gently for the same time interval (3–5 s). Depending on individual ability, the time interval usually starts from 3 s and progresses to 5 s 4 weeks after and 5 s by the end of the interventionRepeat the sequence ten times in one set and perform three sets a day

During the intervention period, frequency measured as times per week differs between groups, as conventional PFMT mainly serves as a supplement to instrumented PFMT for the experimental group. We recommend the same frequency of 3 days a week after the intervention period ends.

After the baseline visit, women in both groups will also get an electronic or printed manual with their personalized PFMT program, emergency contact, and lifestyle advice, such as avoidance of heavy lifting besides breastfeeding and maintenance of unobstructed defecation.

In the subsequent appointments, participants are asked to perform their current program, allowing the physiotherapist to adjust the program according to their progress. Once their PFM strength hits grade 3 in the Modified Oxford Scale, the Knack maneuver will be added. That is pre-contracting PFM against increases in intra-abdominal pressure, represented by coughs in practice. A total of 5 appointments, at the weeks 0, 1, 4, 8, and 12 respectively, will be offered for both groups over the 12-week intervention period.

#### Control group: conventional PFMT

Participants assigned to the conventional PFMT group will perform the prescribed program 3 days a week for the entire intervention period. After each self-managed home-based PFMT session, participants are required to upload a record (note), detailing their contraction and relaxation time for each contractive sequence, repetition of sequences and sets, onto a system checked and responded by physiotherapists on a daily basis. Such recording improves adherence to the intervention, and thereby the control group would acquire the same amount of contact and supervision from medical staff with the experimental group.

#### Experimental group: NMES plus EMG biofeedback

NMES and EMG biofeedback will be performed 24 sessions, two weekly sessions of 30 min with MyoTrac Infinti Encoder (Model SA9800, Thought Technology Ltd., Canada) equipment, which contains two channels for EMG collection, channel A for PFM and channel B for rectus abdominis. NMES is delivered through electrodes on the RAYEE-A Vaginal Probe (Nanjing Vishee Medical Technology Ltd., China). Muscle electrophysiology is collected through electrodes on the same probe at a 14-bit resolution and a 2048-Hz sampling rate. The electric parameters are current type: functional electrical stimulation; frequency: 30–50 Hz; pulse duration: 300–500 μs; time: 10 min; 4–10s cycles; rise: 2–5 s fall: 2–5 s; and stimulation intensity: maximal level tolerable [7, 16]. Participants will be instructed to not actively contract pelvic floor muscles during the electrical stimulation and then perform PFMT following the visual instruction for 15 min. Two NMES and EMG biofeedback-mediated PFMT programs and one conventional PFMT program (see the above section) per week (with 3 PFMTs dispersed in 3 separate days) are arranged for the experimental group to ensure the same total amount of pelvic floor muscle training between two groups.

### Criteria for discontinuing or modifying allocated interventions {11b}

Interventions are suspended when (1) adverse events or other unintended responses occur, (2) more than three procedures and follow-ups are delayed, (3) information is so incompletely collected that it may affect the acquisition and interpretation of the results, or (4) severe protocol deviation and execution error happen. Women intending pregnancy or getting pregnant halfway will no longer receive the intervention. Participants can opt out if they plan on POP surgery. We will meet the participant’s request on discontinuation or group reversal to conventional PFMT. According to their PFM performance, training programs are modified to meet their needs in follow-up appointments.

### Strategies to improve adherence to interventions {11c}

Education on the roles pelvic support plays in POP as well as the impact of its progression on individual lives will be incorporated into the postpartum clinic and research appointments. With controlled training by NMES in the hospital scene and visualization of performance through EMG biofeedback, instrumented PFMT is theoretically motivative in nature. Encouragement from professionals can also raise participants’ self-efficacy. Thus, adherence to conventional PFMT could be enhanced by the timely response to their training records. Monthly calls will enable researchers to monitor their obedience and meanwhile collect encountered obstacles to hopefully overcome by optimizing study design.

### Relevant concomitant care permitted or prohibited during the trial {11d}

Usual postnatal care will continue during the trial.

### Provisions for post-trial care {30}

Usual postnatal care will be maintained after the trial.

### Outcomes {12}

See the “Plans for assessment and collection of outcomes {18}” section for a description on the clinical relevance of each outcome.

#### Primary outcomes

The primary outcome measure is:
The proportion of participants with the improvement of at least one POP-Q stage compared to the baseline data

The primary outcome measure is calculated with each follow-up (M0PI, M6PI, M12PI, M24PI, M36PI, M stands for month, PI stands for post-intervention).

#### Secondary outcomes

The secondary outcome measures include:
The proportion of participants suffering from each symptom at the time of follow-upsThe average decreases in PFDI-20 score, PFIQ-7 score, IIQ7 score, and ED-5Q score and the average increase in PISQ-12 respectively from the baselineThe average grade of PFM strength at the time of follow-upsThe average EMG values in the pre-baseline, flick contraction, tonic contraction, endurance contraction, and post-baseline phases respectively at the time of follow-upsThe average value in the diameter of levator hiatus at the time of follow-ups

The secondary outcome measures are calculated with each follow-up (M0PI, M6PI, M12PI, M24PI, M36PI).

### Participant timeline {13}

See Fig. 2 for the schematic diagram.

**Fig. 2 Fig2:**
[figure not shown]
Content for the schedule of enrolment, interventions, and assessments

### Sample size {14}

Previous research has reported that 43.68~62.8% [31–33] of participants in the electrical stimulation plus PFMT group showed improvement in POP-Q staging while 15.4~20.9% [31–34] showed improvement in the PFMT group. Based on early-stage data from the ongoing pilot study, we estimate the proportion of participants with improved POP-Q stage to be 50% in the experimental group and 20% in the control group. Participants are randomized at a 1:1 ratio to the intervention and control groups. We applied a 2-sample superiority test on the proportions to calculate the sample size by PASS software. Based on our clinical treatment experience, we set the testing margin as 15% which indicates the significant clinical effectiveness. Assuming an attrition rate of 20% by the 36-month follow-up, a sample size of 284 women (142 in each arm) is required in the study to provide more than 80% power at a one-sided significance level of 0.05 for the 2-sample superiority test.

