### Statistical methods

#### Statistical methods for primary and secondary outcomes {20a}

All statistical analyses will be carried out according to the Statistical Analysis Plan and Health Economic Analysis Plan. The primary analysis will be performed at the time right after intervention and at the end of the trial when a 36-month follow-up has been completed. The independent data monitoring and ethics committee (DMEC) will review confidential interim analyses of accumulating data at its discretion, at least annually. The primary effectiveness analysis will be based on the intention-to-treat (ITT) principle.

In the analysis of the primary outcome, we will use the chi-square test to compare the proportion of participants showing improvement of at least 1 level of POP-Q staging among experimental and control groups right after intervention. Furthermore, a binary logistic regression model will be adopted to adjust potential covariate variables like the newborn weight, the length of first/second stage, infant head circumference and the maternal body mass index, etc. For analysis of secondary outcomes, we used appropriate models: the multilevel mixed models for continuous outcomes (PFDI-20, PFIQ-7, PISQ-12, and ICIQ SF-7 scale scores, pelvic floor muscle electromyography values, VAS and QALY of each incremental cost) for the repeated measurements at 6, 12, 24, and 36 months, chi-square test and logistic regression for categorical outcomes (POP-Q staging, pelvic floor muscle strength). The safety index (AE incidence) was analyzed with the chi-square test.

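### The sample size is calculated for a one-sided test against a 15-point margin, but the primary analyses named in the protocol carry no margin, so the stated power does not describe them

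*Protocol article*

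**What the plan says.** Protocol article, Sample size {14}: the expected rates are given as "we estimate the proportion of participants with improved POP-Q stage to be 50% in the experimental group and 20% in the control group". The method is described as "We applied a 2-sample superiority test on the proportions to calculate the sample size by PASS software", and on the margin the section says "we set the testing margin as 15% which indicates the significant clinical effectiveness". The loss allowance is worded "Assuming an attrition rate of 20% by the 36-month follow-up", and the result is 284 women, 142 per arm, for "more than 80% power at a one-sided significance level of 0.05 for the 2-sample superiority test".

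Protocol article, Statistical methods {20a}: for the primary outcome, "we will use the chi-square test to compare the proportion of participants showing improvement of at least 1 level of POP-Q staging", with the comparison placed right after the intervention. A logistic model is added for covariate adjustment. The same section puts the primary analysis at two times, right after the intervention and at the end of the 36-month follow-up.

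Protocol article, Abstract (Methods): chi-square is assigned to the post-intervention comparison and multilevel mixed models to the follow-up until 36 months.

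The margin and the one-sided 0.05 level appear only in {14}. The only significance level given for any analysis is 5%, with sidedness unstated, in the subgroup section {20b}.

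**The concern.** A superiority test by a margin and an ordinary chi-square test answer different questions. The first asks whether the experimental arm is better by more than 15 points, the second whether the arms differ at all. If the number of women comes from the first and the analysis is the second, the stated power is not the power of the planned test.

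The sponsor has also declared that 15 points marks clinical effectiveness, yet no described analysis compares the result with 15 points. Two readers could then judge the same data differently, one by the p-value against zero and one by the margin. Nothing in the protocol article settles in advance which of them is right.

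**Working it through.** **Inputs.** From {14}: experimental rate 0.50, control rate 0.20, margin 0.15, one-sided alpha 0.05 (z = 1.645), power 0.80 (z = 0.842), attrition 20%, allocation 1:1. From {20a}: chi-square test with no margin. Assumed, because {20a} does not say: two-sided 0.05 for the chi-square test. Normal approximations are used throughout.

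**1. Reproduce the plan's figure.** With the margin shifting the null and unpooled variance:

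n per arm = (1.645 + 0.842)² × (0.50×0.50 + 0.20×0.80) / (0.30 − 0.15)² = 112.7, so 113.

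113 / 0.80 = 141.25, so 142 per arm and 284 in total. This matches {14} exactly.

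**2. Is the margin really in the calculation?** Without it, the same rates need (pooled variance under the null, pooled rate 0.35):

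n per arm = [z × √(2×0.35×0.65) + 0.842 × √0.41]² / 0.30²

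This gives 39 per arm for z = 1.960 (two-sided) and 31 for z = 1.645 (one-sided), before attrition. Neither leads to 284. The margin is part of the null hypothesis that was sized.

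**3. Power at 50% v 20% with 284 randomised** (142 × 0.80 = 113.6 evaluable per arm; standard error √(0.41/113.6) = 0.0601):

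- Margin test: Φ(0.15/0.0601 − 1.645) = Φ(0.852) = 80.3%. This is the power that {14} states.
- Chi-square, two-sided 0.05: null standard error √(2×0.35×0.65/113.6) = 0.0633; Φ[(0.30 − 1.960×0.0633)/0.0601] = Φ(2.93) = 99.8%.

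**4. Smallest significant result, 113 per arm, control at 23/113 (20.4%):**

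- Chi-square: 36/113 (31.9%), a difference of 11.5 points, 95% CI 0.2 to 22.9.
- Margin test: 52/113 (46.0%), a difference of 25.7 points.

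**5. Chance of rejection when the true effect does not exceed the margin, about 113 per arm:**

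| True rates | Chi-square, two-sided 0.05 | Margin test, one-sided 0.05 |
|---|---|---|
| 35% v 20% (exactly 15 points) | about 72% | about 5% |
| 30% v 20% (10 points) | about 41% | under 1% |

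If the chi-square were read one-sided at 0.05, the 72% would be about 82%.

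**6. What the margin test would deliver under the protocol's other rules.** Section {20c} says that missing primary-outcome data take the baseline value for reference. If this means baseline carried forward, women lost to follow-up count as not improved. With 20% lost, the rates become 0.50×0.80 = 40% and 0.20×0.80 = 16%, a difference of 24 points with all 142 per arm analysed:

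standard error = √[(0.40×0.60 + 0.16×0.84)/142] = 0.0513; power = Φ[(0.24 − 0.15)/0.0513 − 1.645] = Φ(0.108) = about 54%.

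Separately, the Abstract, Trial design {8} and Sequence generation {16a} give 274 rather than 284. On completers that is 137 × 0.80 = 109.6 per arm, and the margin test has Φ(0.808) = 79.0% power, just under the level claimed.

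**The case against.** Four points can be made on the other side.

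- **The SAP may contain the margin test.** {20a} defers to an SAP that is not shown, and an article commonly leaves the form of the hypothesis and the decision rule to it. A reader might infer that the margin test will never be run, but the documents do not support that. What stands is narrower: the protocol names a primary test, and it is not the one that was sized.
- **No success rule is stated.** A reader might also infer that the sponsor will declare success below 15 points. That assumes a chi-square p-value below 0.05 would be read as success, which no section says. It is a natural reading of a named primary test, but only a reading.
- **The chi-square test belongs to another visit.** The sizing allows for attrition by 36 months, whereas the chi-square is placed right after the intervention. So 113 evaluable per arm is illustrative for that visit, where fewer losses would be expected. The objection does not remove the mismatch, because the mixed models named for the follow-up carry no margin either.
- **The trial is not underpowered for the chi-square test.** This is correct. The test remains valid for a zero difference, and a reported risk difference with its interval would let a reader judge the 15 points. The harm is a power statement for a different test and an unclear meaning of a positive result, not bias or lack of power.

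**Conclusion.** The concern holds in this form: the figure of 284 is arithmetically right for a one-sided 0.05 test against 15 points, and no primary analysis named in the protocol article carries that margin or that level. The stated power of just over 80% should read about 99.8% for the named chi-square test at the design rates. That test can be significant at less than half the observed difference that the margin test requires (11.5 v 25.7 points).

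These sizes assume about 113 evaluable women per arm, a control rate near 20%, two-sided 0.05 for the chi-square and normal approximations. The conclusion that sizing and named analysis test different hypotheses needs none of these assumptions.

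**What to change.** State one primary hypothesis, one time point, one alpha and one sidedness, in the same words in {14} and {20a}. Then choose one of two routes. The choice is the sponsor's.

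- **(a) Superiority to zero.** Remove the margin from {14}, restate the power for the zero-difference test (about 99.8% at two-sided 0.05 with about 113 evaluable per arm), and report the risk difference with its confidence interval against 15 points. The cost is a restated power and a sample size whose justification must be rewritten.
- **(b) Superiority by the margin.** Make the primary analysis a test of the risk difference at the named time point, with success if the lower limit of the two-sided 90% confidence interval exceeds 15 points. The zero-difference chi-square can stay as supportive.

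Route (b) is not a change of wording alone. Before adopting it, restate its power for the missing-data rule in {20c} (about 54% if losses count as not improved) and for the number actually to be enrolled (79% on completers at 274). The cost is a stricter success criterion and a lower stated power. Either change should be made before outcome data are analysed by arm.
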